## Abstract

Currently one-third of children in the United States have overweight or obesity (OW/OB). The goal of Healthy People 2020 is to reduce the proportion of children with OW/OB and increase the proportion of primary care visits that include nutrition and weight-related counseling. Unfortunately, many health care providers find it difficult to offer effective weight-related counseling and treatment in the primary care setting. Therefore, new models of care are needed that allow a greater proportion of children with OW/OB and their parents to access care and receive quality weight management treatment. The current paper describes the GOT Doc study which is designed to test the effectiveness of a Guided Self-Help (GSH) model of obesity treatment that can be delivered in the primary care setting compared to a traditional Family-Based Behavioral weight loss treatment (FBT) delivered at an academic center. We will assess the impact of this program on attendance (access to care) and changes in child BMI percentile/z-score. We will also examine the impact of this treatment model on change in child lifestyle behaviors, parent support behaviors, and parent self-efficacy and empowerment to make behavior change. Finally, we will assess the cost-effectiveness of this model on changes in child BMI percentile/z-score. We believe the GSH intervention will be a cost-effective model of obesity management that can be implemented in community practices around the country, thereby increasing access to treatment for a broader proportion of our population and decreasing rates of childhood obesity.

## Introduction

1

Currently, one in three children in the United States aged 6–19 years have overweight or obesity, with higher rates among Hispanic and African-American children [1]. Because of the many medical and social co-morbidities [[2], [3], [4], [5], [6]] children with overweight/obesity (OW/OB) incur greater medical costs from frequent lab studies [7], sick visits, and utilization of mental health services [8]. While prevention is necessary, widely available and effective treatments are also needed to help those who are already on the path towards greater health care utilization.

The goal of Healthy People 2020 is to decrease the proportion of children with OW/OB and increase the proportion of primary care visits that include nutrition and weight-related counseling [9]. The Early and Periodic Screening, Diagnosis, and Treatment program (EPSDT) for children enrolled in Medicaid also recommends nutrition counseling at each well-child visit [10]. While primary care providers (PCPs) have been identified as key players in the treatment and prevention of obesity by several national groups [[11], [12], [13]] they often report low confidence in their ability to counsel on this topic, as well as a lack of time and resources [14,15]. The U.S. Preventive Services Task Force (USPSTF) has also noted that moderate intensity counseling may not be deliverable by PCPs within the confines of the current well-child visit, and that these children should be referred to intensive counseling or behavioral interventions to assist with weight loss [16]. Thus, if we are to follow national mandates to provide easily accessible and effective obesity-related treatment, other care models need to be developed.

Current gold-standard treatment for obesity involves family-based behavioral therapy (FBT). These programs are intensive, requiring up to 26 h of treatment over 6 months, and are typically located at tertiary care academic centers. However access to these programs can be difficult due to limits on capacity and location [17]. Furthermore, lack of flexibility in scheduling makes it difficult for families to attend weekly group sessions [17]. In one study, only 28% of the families who were offered this treatment enrolled, and only 63% of those families completed the intervention [18].

We developed a Guided Self-Help (GSH) model of obesity management which is shorter in duration, could be delivered in the primary care setting, and has been shown to be equally effective as FBT [19]. GSH provides structured behavioral management for obesity treatment and is designed as a practical tool for health care providers to implement in the primary care office. Although the program is self-directed, GSH programs offer structure to promote treatment compliance and application, as is suggested by the Expert Committee Recommendations for Stage 2 treatment [12]. Frequency and intensity of visits are also realistic for the primary care setting and resembles Medicare coverage for adults.

The goal of this study is to test whether implementation of a GSH model of obesity treatment in the primary care setting can increase access for families to effective obesity treatment and decrease child BMI percentile/z-score. Given the need to increase access and availability of effective obesity treatment in the community, this intervention may provide useful information regarding the structure of such efforts.

## Study objectives

2

The goal of the GOTDoc (**G**uided self-help **O**besity Treatment in the primary care setting) study is to test the effectiveness of the GSH model of obesity treatment compared to usual care (family-based behavioral weight control treatment (FBT) in a tertiary care setting) in 200 families with children with OW/OB between the ages of 5 and 13 years old. Research staff or health coaches will deliver GSH in the primary care setting and FBT at the UC San Diego Center for Healthy Eating and Activity Research (CHEAR). The intervention and data collection will occur from January 2017 to December 2019. Primary outcomes will include the proportion of treatment sessions families attend (GSH vs. usual care) and change in child BMI percentile/z-score. Secondary aims will include examination of change in child lifestyle behaviors, parent support behaviors, and parent self-efficacy and empowerment to make behavior changes. Cost-effectiveness of GSH on changes in child BMI percentile/z-score is also a secondary outcome. We hypothesize that there will be greater attendance of treatment in the GSH arm, and that among those who attend treatment, there will be similar changes in weight status between groups. However, because more families will attend GSH, we also hypothesize that in the intent to treat analysis GSH will have a greater impact on child BMI percentile/z-score than usual care (FBT). We also hypothesize that GSH will be more cost-effective than FBT.

## Study design

3

### Trial design

3.1

GOTDoc is a two-arm, parallel assignment, pragmatic clinical trial, using a randomized control design, comparing GSH delivered in the primary care setting to traditional FBT delivered in an academic center. The intervention will be implemented in the Children's Primary Care Medical Group of San Diego (CPCMG). Two CPCMG sites with 6 providers at each site were identified in San Diego that have similar socio-economic and ethnic/racial demographic characteristics among their patient population. Parent and child will be randomized within each clinic at a one-to-one ratio to receive GSH at the clinic or intensive FBT for weight loss at CHEAR. Randomization will occur at the level of the individual, allowing us to eliminate the effect of the provider on treatment effects. Randomization will also be stratified by child sex to ensure equal distribution between groups. Assessments will occur at baseline, post-treatment (month 6), and 6-month follow-up (month 12). The primary outcomes of this study are attendance and change in BMI percentile/z-score. Secondary outcomes are change in child lifestyle behaviors, parent support behaviors, and parent self-efficacy and empowerment to make behavior change. We will also examine the cost-effectiveness of the GSH model of treatment on changes in child BMI percentile/z-score.

### Participants

3.2

Participants in this study will include 5–13 years old children with an age and gender adjusted BMI ≥85th percentile, and their parent or guardian (hereafter referred to as parent). Parents may be normal weight, overweight, or obese. The communities from which these samples will be drawn are largely Hispanic (48.9%–58.2%), with a median income ranging from $49,787 to $65,364, 18.3%–10.4% living below the poverty level, and 73.3%–81.9% with a high school degree or higher. The prevalence of childhood obesity in these neighborhoods ranges from 38.9% to 37.9% [20].

### Inclusion/exclusion criteria

3.3

Inclusion criteria for this study are: 1) a child between the ages of 5 and 13 years old with a BMI ≥85th percentile for age and gender; 2) parent who is responsible for food preparation willing to participate; 3) parent who can read English or Spanish at a minimum of a 5th grade level; 4) family who is willing to commit to attendance at all assessment visits; and 5) family not moving out of the San Diego area within the time frame of the study. Because this is a pragmatic clinical trial, and to allow for examination of heterogeneity of treatment effects and generalizability, limited exclusion criteria will be applied. However, a few criteria will be applied, including: 1) child who is taking medication that may impact weight; 2) child with physical difficulty that limits his/her ability to exercise; and 3) child with a medical condition for which physician supervision of diet and exercise prescription are needed. Children with a diagnosis of a behavioral or psychiatric disorder (based on parent report), but who have been stable on medication for at least 6 months or engaged in therapy, will be allowed to participate in the program as long as they are potentially able to participate in a group setting.

### Recruitment and retention

3.4

Children with OW/OB and their parent will be identified in the electronic health record (EHR) based on the child's BMI percentile. PCPs will discuss obesity management with the family (to the extent that they would normally do) and then refer them to the study coordinator via the EHR if the family is interested in participating in a weight control program. The study coordinator will be in the office several days of the week to increase recruitment capacity and conduct the screening and consent process. When the study coordinator is not in the office, she will call the family, screen them for eligibility, and obtain additional demographic and medical history information. Families eligible and interested in the study will be invited back to the office to complete the consent process. If more than one child in the family meets study criteria, the study coordinator will use a random numbers table to select the index child for data collection. However, both children will be able to participate in treatment if they are within the study age range. The parent will complete the consent process and form, and any child age 7 years or greater will provide assent to participate and complete an assent form. This study was approved by the Institutional Review Board of the University of California, San Diego.

After the consent process, eligible families will complete assessments. Parents and children will complete online or paper surveys. Families still in the office will have their height and weight measured, otherwise families will return at a later time to obtain a research height and weight. In order to ensure high retention of our sample, we will request personal e-mail addresses and cell phone numbers as well as contact information for two close friends/relatives to enhance our ability to maintain contact with our participants. All families will receive $25 for each of the baseline, 6-month and 12-month assessments as compensation for time and effort. A systematic protocol will be followed to minimize subject attrition at the assessment visits. Participants will be scheduled by telephone, sent e-mail reminders, and called or sent a text reminder the day before the visit. Missed assessment visits will be rescheduled and followed up at least three times. If necessary, transportation to the clinic will be provided. For treatment visits, a similar reminder system will be used.

### Assessment and outcomes measures

3.5

All assessments will occur at baseline, post-treatment (month 6), and 6-month follow-up (month 12). Both parents and children will participate in these assessments. Assessments will include anthropometry and self-report questionnaires. Parents participating in the study will be asked to complete assessments on their readiness to engage in weight control behaviors [21,22], self-efficacy to lose weight [21,23], and empowerment to access resources for healthy weight [24]. Parents will also report on their behaviors that support child weight loss efforts [25], and potential self-regulatory mediator variables such as goal setting and adherence to GSH recommendations [[26], [27], [28], [29], [30], [31], [32], [33], [34]]. Finally, parents will report on their child's dietary and physical activity behaviors, and provide information on resources utilization for the cost effectiveness analysis. Medical record abstraction will occur at the end of the study to obtain additional information regarding documented anthropometrics and health care utilization. Data collection will be conducted by trained staff and supervised by the principle investigator.

### Measures

3.6

#### Measurements (Table 1)

3.6.1

Anthropometry (child and parent). Child and parent height will be measured using a portable Schorr height board (Schorr Inc, Olney, MD) in duplicate. Height will be recorded to the nearest 0.1 cm for both trials, and the average of the 2 values used for analysis. Body weight in kilograms will be measured in duplicate on a Tanita Digital Scale (model WB-110A). Body weight will be recorded to the nearest 0.1 kg and the average of the 2 values used for analysis. Height and weight will be converted to body mass index (BMI = [kg/m2]). Since children are growing, BMI will be translated to BMI for age percentile score using the CDC growth charts [35,36] and to standardized age and gender referenced BMI (BMI Z-scores) [37].

**Table 1 tbl1:** Schedule of assessments and measures.

	Measure	Baseline	Post-treatment	6-Month Follow-up
Anthropometry	Height/Weight	X	X	X
Demographics	Demographics and Medical History questions	X		
Parent assessments	Parent Importance, Confidence, & Readiness questionnaire [21] Lifestyle Behavior Checklist (Confidence scale) [23] Parent Resource Empowerment Scale [24] Activity Support Scale [25]	X X X X	X X X X	X X X X
Child Lifestyle Behaviors	Dietary History and Eating Behaviors Godin Leisure Time Exercise Questionnaire [41]	X X	X X	X X
Parent support & weight control behaviors	Frequency of self-monitoring behaviors		X	X
	Parent report of adherence to treatment recommendations		X	X
Enrollment/attendance, Treatment Adherence, Acceptability	Enrollment and Attendance (weekly assessment) Self-monitoring in habit books (weekly assessment) Acceptability		X X	X X X
Cost-effectiveness	Family utilization & cost data Administrative data	X X	X X	X X

Demographic Characteristics (baseline only). At the baseline assessment, parents will complete demographic questionnaires that include items on racial/ethnic identity, sex, income, education, marital status, health history, and medication use.

Parent Importance, Confidence, and Readiness for Change Questionnaire: This questionnaire is a self-report measure that assesses motivation for behavioral lifestyle change. It contains three subscales: importance of change, confidence to make changes, and readiness to change. In a weight control study for children age 7–13 years old and their parents, parental confidence predicted premature participant dropout, early treatment response (5-week child weight loss) and child weight loss at post-treatment [21].

The Lifestyle Behavior Checklist (LBC) — Confidence Scale: The LBC lists 25 weight-related problem behaviors in children aged 4–11 years (e.g., eating too much, watching too much television, complaining about doing physical activity) [23]. For the Confidence scale, parents are asked to rate how confident they feel in managing each of these behaviors (even if not currently occurring) on a 10-point scale. The resultant score is a measure of lifestyle-specific parenting self-efficacy. The LBC Confidence scale has very high internal consistency (α = 0.97) and acceptable test-retest stability (r^s^ = 0.66).

Physical activity-, Diet-, and Weight-related Resource Empowerment scale. This 15-item scale was adapted from the Sprietzer Empowerment Scale [38], and is used to assess parent empowerment around accessing resources for child weight, physical activity, and diet behaviors. The scale assessed empowerment in each of these three domains, asking 5 questions around knowledge of resources, ability to access resources, comfort accessing resources, knowledge of the strategies needed to identify new resources, and ability to obtain those resources. A 4-point scale was provided for the response choices (1 = strongly disagree, to 4 = strongly agree). The scale exhibits high internal consistency with internal reliability scores ranging from *α* = 0.93 to 0.97 [24].

Activity Support Scale for Multiple Groups (ACTS-MG): The ACTS-MG is a 12 item scale that was modified from the original Activity Support Scale [39,40] and tested in multiple racial/ethnic groups. The scale consists of three subscales: logistic support, modeling, and use of community resources. Internal consistency coefficients were acceptable for each subscale ranging from *α* = 0.69 - 0.88 [25].

Dietary History and Eating Behaviors: A dietary history and eating behaviors questionnaire was developed to reflect the dietary recommendations that are made in the GSH and FBT interventions. Parents were asked to reflect on their child's eating behaviors in the last week. Sample questions included: frequency of eating breakfast, consuming sugar sweetened beverages, consuming sweet or salty snacks, consuming 4–5 servings of fruits and vegetables per day; frequency of plating your child's dinner; limiting seconds during a meal; use of a measuring device during meal prep; removing high calorie foods from the house; and removing screens from the kitchen. Response choices involving frequency of eating behaviors during the week included: ‘0–7 days’ or ‘never’ to ‘5 or more times per day’. Parents were also asked to report on average daily portion of fruits and vegetables (asked separately) were consumed per day. Five-point likert scales (0 = never to 5 = always) were also used to ascertain how often a specific stimulus control behavior was used during the week.

Godin Leisure-time Exercise Questionnaire: The Godin Leisure-time Exercise Questionnaire [41] assesses the frequency and occurrence of leisure time physical activity. It asks participants to report the number of times during a typical week they participate in mild, moderate and strenuous exercise for more than 15 min. The Godin Leisure-time Exercise Questionnaire correlates with objective indicators of exercise and physical fitness, and has been shown to be a reliable and valid measure of leisure-time exercise [42].

Treatment adherence and acceptability: In both arms, attendance at treatment sessions, adherence to treatment recommendations, and self-monitoring behaviors (percent of days monitored) for child and parent will be collected using daily habit books and food diaries. Questionnaires developed by the research staff will be administered at the end of the study to assess parent and child liking of the program, engagement in specified behaviors, and any concerns or barriers they had during the program. Additional information will be gathered regarding liking of the condition assignment (GSH vs. FBT).

Medical Record Abstraction: At the end of the study period, de-identified information on patients with OW/OB who signed consent but did not complete the assessment or enrollment process will be obtained to determine if there were differences between those who enrolled vs. those who did not. For those enrolled in the study, information will be gathered regarding frequency of patient weight-related visits (to the PCP or a dietitian) and other health care utilization (including referrals, medications, hospitalizations).

Cost-effectiveness measures. Cost effectiveness is of interest in this trial due to the potential to replicate the proposed GSH model in other primary care settings. The primary perspective for this cost effectiveness analysis will be the societal perspective which captures the broadest range of costs that are pertinent [43]. From a societal perspective, the delivery costs for the intervention arm will include reproduction of intervention study materials, distribution of study materials, intervention staff/coaching time for counseling and follow-up, administrative staff time, patient time and expenditures to receive the intervention, and IT support. Research development and research related overhead costs will be excluded from the estimate of the intervention costs.

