Dietary recommendations. GSH utilizes the Traffic Light Diet, which categorizes food by energy content into the three colors of the traffic light. Foods are classified into red, yellow and green based on caloric density and grams of sugar per serving; green foods (go) are low in calories and may be consumed in unlimited quantities; yellow foods (caution) have average nutritional value for foods within their food group and are to be eaten with caution; red foods (stop) are energy-dense and should be limited in quantity [[51], [52], [53], [54]]. Dietary recommendations encourage parents/children to count the number of servings consumed for each traffic light color (red, yellow and green). All reductions in energy intake are shaped over time and decreases in consumption of red foods are reinforced. Children will be encouraged to consume 1000–1200 kcals per day while parents will be encouraged to consume 1200–1400 kcals/day. Additional goals include increasing the number of family meals eaten together and increasing vegetable and fruit consumption.

Physical activity recommendations. GSH recommends increasing both lifestyle activity and structured exercise programs [[55], [56], [57]]. Lifestyle activity goals focus on building increased activity into typical, daily activities, such as walking or bicycling to school, and structured exercise goals stimulate routine, planned exercise. Parents and children are also instructed to decrease sedentary behaviors, such as TV watching, video games or computer usage outside of schoolwork. The goal is to engage in 90 min of physical activity on 5 out of 7 days of the week for children and at least 60 min on 5 out of 7 days of the week for parents.

Behavior change recommendations. Key elements of behavior therapy are provided in GSH, including stimulus control, self-monitoring, goal setting and contracting, strategies for managing high-risk situations, relapse prevention skills, and parent management skills training [58]. Self-monitoring is a fundamental aspect of self-regulation and includes observing and recording of eating and exercise behavior, and has been related to weight loss in children and adults [[59], [60], [61], [62], [63]]. In GSH, parents and children will receive “Habit Books,” and are instructed to record their dietary intake and physical activity each day. During each session, the health coach will review habit books and reinforce families for their efforts at any self-monitoring.

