### Usual care control group: family-based behavioral therapy (FBT) for pediatric weight loss

4.3

Families randomized to the usual care group will be referred to the tertiary care FBT weight control program offered at CHEAR. The tertiary care program is based on the gold-standard FBT for pediatric weight loss [[65], [66], [67], [68]] and includes the same nutrition and physical activity education as well as behavioral strategies delivered in GSH. However, families in FBT will attend 16-weekly, and then 4 bi-weekly group sessions over a 6-month period at our site in La Jolla. Group sessions are conducted separately for parents and children and last 60 min each week. Both parents and children will receive weekly age-appropriate manuals and activities to do at home. Families may continue to follow-up with their PCP (time frame to be determined by the PCP) to follow anthropometric changes.

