## Data analysis

5

5.1. This study is a pragmatic randomized control trial using a one-to-one randomization ratio within each clinic, randomizing at the level of the individual. First, we will track the number of sessions each family attended within each group and examine if there is a difference in the proportion of sessions attended between groups using a generalized linear model (binomial family). For our second primary outcome, we will estimate between-group differences (GSH vs FBT) in BMI percentile/z-score (our second primary outcome) over 6- and 12-month assessments using linear mixed effects (LME) analysis adjusting for corresponding baseline BMI percentile/z-score values. BMI z-score is calculated using the formula: [(BMI/M)^L^ −1]/(L x S). (M = median; L = power in the Box-Cox transformation; S = generalized coefficient of variation; values vary based on age in months of the child) All models will adjust for standard patient characteristics (age, race/ethnicity, sex, insurance type) as planned covariates and any differential effects across clinics (i.e., main effect rather than random effect given limited number of clinics).

As a secondary analysis, we will assess the degree to which treatment assignment (GSH vs. FBT) was associated with change in proposed mediators (considered outcomes in these analyses) including child lifestyle behaviors (e.g., eating and physical activity behaviors), parent self-efficacy, parent empowerment, and parent support behaviors (e.g., parent monitoring, adherence to treatment recommendations) using LME models. For mediation modeling, we first will estimate the effect of allocation on a change in proposed mediators (path ‘a’) at 6-months with adjustment for corresponding baseline values. If significant, we will then add baseline and 6-month terms for mediators to the LME model examining their relationship to the primary outcome of BMI percentile/z-score. The indirect effect of group allocation on BMI percentile/z-score through changes in mediators (path ‘b’) will be computed using a product of coefficients method (path ‘a*b’) along with bootstrap confidence intervals. As an adjunct to the primary analyses, we will also explore attendance patterns using a cox proportional hazards regression model to examine predictors of attrition, defined as missing 3 or more consecutive sessions.

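### Section 3.6.1 names habit books and food diaries as the source for attendance, the first primary outcome, which fits poorly with Table 1 and sections 4.2 and 5.1

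*Protocol article*

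**What the plan says.** Section 2 makes attendance a primary outcome: "Primary outcomes will include the proportion of treatment sessions families attend (GSH vs. usual care) and change in child BMI percentile/z-score".

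The paragraph on treatment adherence and acceptability in section 3.6.1 gives the data source. Its list begins "In both arms, attendance at treatment sessions, adherence to treatment recommendations, and self-monitoring behaviors (percent of days monitored) for child and parent will be collected", and the sentence closes with "self-monitoring behaviors (percent of days monitored) for child and parent will be collected using daily habit books and food diaries". Grammatically, the books and diaries are the source for all three items: attendance, adherence and self-monitoring.

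Three other places bear on the same point:

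- Table 1 has separate entries for attendance and habit-book monitoring: "Enrollment and Attendance (weekly assessment) Self-monitoring in habit books (weekly assessment) Acceptability".
- Section 4.2 says what goes into the books. Parents and children "are instructed to record their dietary intake and physical activity each day". It mentions no entry for session attendance.
- Section 5.1 says of the first primary analysis that "we will track the number of sessions each family attended within each group", without naming a record.

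Section 5.3 adds that primary outcomes will be analysed in participants who gave both a baseline and a post-treatment assessment.

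**The concern.** A family-kept diary is a poor source for a count of sessions. If a book is blank, lost or left at home, it cannot separate a family that stayed away from one that came and had not recorded. The first primary comparison needs exactly that distinction. So does the exploratory Cox model in section 5.1, which defines attrition by three or more consecutive missed sessions.

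The sentence in section 3.6.1 is a positive statement about the data source, so it cannot be treated as detail left to a fuller protocol or analysis plan. Staff who followed it would be collecting the first primary outcome with an instrument designed for something else.

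Families who never start are a related difficulty. They have no book, and they may well be the families who miss the post-treatment visit. Under section 5.3 they could drop out of the attendance analysis altogether, although their attendance is known to be 0 and the hypothesis in that section concerns entering treatment as well as attending it.

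**Working it through.** **1. The texts side by side.** Section 3.6.1 assigns attendance to the books and diaries. Section 4.2 gives the books a different content. Table 1 names habit books for self-monitoring only. Section 5.1 implies a count kept by the study. Neither Table 1 nor section 5.1 names an instrument, so the diary sentence is the only stated source, and it is the one that does not fit the rest.

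**2. The plan's own figure.** Inputs from section 5.3: attendance above 85% in GSH (taken as 0.85) and 60% in FBT, 100 families per arm, up to 20% lost (80 per arm), two-sided alpha 0.05. With the family as the unit and p̄ = (0.85 + 0.60)/2 = 0.725:

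power = Φ{ [ |p1 − p2| − 1.96·√(2p̄(1 − p̄)/n) ] / √([p1(1 − p1) + p2(1 − p2)]/n) }

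- n = 100: (0.25 − 1.96 × 0.06315)/0.06062 = 2.08, power 0.981.
- n = 80: (0.25 − 1.96 × 0.07060)/0.06778 = 1.65, power 0.950.

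The stated power above 0.95 is reproduced.

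**3. What under-recording could do.** The document gives no capture rate, so every rate here is an assumption. The illustrations show only that the effect depends on unknown rates.

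- Equal capture in both arms, 100 per arm: at 90%, 0.765 vs 0.540, power 0.92; at 80%, 0.68 vs 0.48, power 0.82; at 70%, 0.595 vs 0.420, power 0.70.
- Unequal capture, 95% in GSH and 85% in FBT: 0.85 × 0.95 − 0.60 × 0.85 = 0.8075 − 0.51 = 0.2975, so the 25-point difference is recorded as 29.75 points.
- The reverse, 85% in GSH and 95% in FBT: 0.7225 − 0.57 = 0.1525, recorded as 15.25 points.

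The sign of the error changes with the assumption, and nothing in the document selects one.

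**4. Families who never start.** Suppose FBT attendance over all 100 randomised families is 60%, and the 20% allowed as lost are all families who never came (an extreme assumption). The remaining 80 then average 60%/0.80 = 75%. Restricting the analysis to families with a post-treatment assessment would report 75% where the all-randomised figure is 60%. The effect on the between-arm difference depends on the corresponding number in GSH, which is also not given.

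**The case against.** The strongest reply is that section 3.6.1 is a compressed list. On that reading the diaries belong to adherence and self-monitoring, and attendance is counted by staff, as section 5.1 and Table 1 suggest. Research staff or health coaches deliver both treatments (section 2), and all sessions are audiotaped (section 4.4), so an attended session would hardly go unnoticed. This is probably what the sponsor intends. But none of these places says that staff keep the attendance record, and the one sentence that names a source names the diaries.

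A reader might infer more: that capture differs between arms in favour of GSH. In GSH, "During each session, the health coach will review habit books and reinforce families for their efforts at any self-monitoring", whereas section 4.3 says of FBT only that "Both parents and children will receive weekly age-appropriate manuals and activities to do at home". The document does not support that inference. The sentence in section 3.6.1 applies to both arms, section 4.3 says FBT includes the behavioural strategies used in GSH, and silence about book review in a condensed article is not evidence of unequal recording.

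Nor is attendance shown to be merged with self-monitoring. Section 3.6.1 measures self-monitoring separately, as the percentage of days monitored, and Table 1 gives it its own entry.

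It can also be said that a missing book does no harm for a family that never starts, because the right value is 0. That holds if the blank is scored 0 and the family stays in the analysis, but the restriction in section 5.3 leaves this open.

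**Conclusion.** The point holds as an inconsistency about the source data of the first primary outcome. The one stated source suits the outcome badly and fits poorly with Table 1 and sections 4.2 and 5.1. Taken literally, it allows attended sessions to go unrecorded.

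It is not a demonstrated bias. No direction or size can be given, because the document states no capture rate and does not show a difference between arms. No stated number is wrong. The figures for under-recording and for families who never start rest wholly on assumed rates. The point still deserves correction, because it concerns a primary outcome and the wording can be settled at almost no cost.

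**What to change.** In section 3.6.1, remove attendance from the habit-book sentence and keep the books and diaries for self-monitoring and adherence. Then state that in both arms:

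- attendance is taken from a session log completed by the coach or group leader;
- the denominator is all scheduled sessions, 14 in GSH and 20 in FBT (16 weekly plus 4 every other week);
- every randomised family is included, with those who never start counted as 0, whether or not they give a post-treatment assessment.

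The last item needs a matching qualification in section 5.3, so that its requirement for both assessments does not govern the attendance analysis. The cost is a few lines of text and a sign-in log kept by staff who already run every session, with no extra visits or personnel.
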